### Blinding

Due to having a control group which receives no intervention, blinding cannot be performed for all groups. But in try to blind intervention and placebo controlled group, vitamin suppositories and placebo suppositories will have the same color and shape and will coded as A and B by a pharmacologist not involved in the research team. The researchers will receive the suppositories with codes and will not know what A and B stands for with respect to the suppositories. Finally, after collecting questionnaires and analyzing data using SPSS version 25 software, the codes that belong to the groups will be determined.

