**Methods:**

In a randomized, controlled clinical trial, 105 postmenopausal women will be randomly assigned to three groups receiving vitamin D vaginal suppository, placebo vaginal suppository, or control (no intervention). Vitamin D vaginal suppositories contain 1000 units of vitamin D3. The timing of the use of vitamin D vaginal suppositories and placebo suppositories will be every night in the first 2 weeks, and every other night in the following 6 weeks (8 weeks in total). The primary outcome will be the sexual function of participants which will be assessed using the Female Sexual Function Index (FSFI) before and immediately after the intervention, and at 1 and 2 months after the end of the intervention. The side effects of these suppositories will be examined as a secondary consequence of the study. Data will be analyzed using SPSS software version 25. In the case of normal distribution of data, the mean score of sexual function will be compared between the groups using a repeated measurements ANOVA. If statistical analysis leads to significant results, the post-hoc test will be used to determine the differences between the groups. Comparison of demographic and fertility characteristics of the women will be carried out using statistical tests such as chi-squares and *t*-tests. A significance level of *p* < .05 will be used for statistical analyses.

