### Sample size estimation

According to previous study by Çayan et al. [32], considering α = 0.05, power = 80%, moderate effect size 0f 0.6, the sample size for the research study was estimated to be 25 people for each group. Considering the attritional loss of 40% of the samples in the research process, the sample size for each group was calculated to be 35 people. The sample size calculation was performed according to primary outcome of study.

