### Randomization

The participants will be randomly assigned into the study groups. Random allocation will be carried out using the simple randomization method, and assignment sequences will be written on paper before the start of the research as either A (suppository of vitamin D3 group), B (placebo suppository group), and C (control group without intervention). Randomization will be performed using random allocation software. The type of intervention will be written in accordance with the assignment sequence and will be enclosed within the opaque envelopes. Questionnaires will be also encoded in sequence. In this case, the questionnaire with the same code will be completed for the person receiving the code 1 intervention.

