### Intervention program and patient education

During the first visit, the vaginal suppositories (without identifying the type of suppository, only having an identifier code inside the appropriate envelopes) will be given to the participant. The method and duration of use, as well as the follow-up time will be taught by the researcher to each participant. A phone number will be provided to ensure that the supplements are properly used and participants will reminded to keep track of the follow-up time. The researcher’s phone number will be shared with the participants to contact them if they have any questions about how to use the suppositories and/or if they experience any problems or signs of burning and itching following the use of the suppositories. As noted above, the total time period to take the suppositories for each postmenopausal woman will be 8 weeks, during which the investigator will monitor the use of the suppositories in the women by telephone or text-messaging (based on the convenience of the participant).

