### Safety issues

Overall, the total intake dose of vitamin D3 will be 32,000 units during the 8 weeks of the intervention. The risk of poisoning with vitamin D is due to an overdose of vitamin D3 is 50,000 units per month (according to the Iran’s national guidelines) if administered over a long period of time. Given that the overall dose used in the proposed study is much lower than the level considered by the country’s guidelines, the probability of poisoning is low. In addition, to address concerns about the likelihood of poisoning with vitamin D3, the participants would be asked to withdraw taking supplemental vitamin D3 during the study. In addition, all symptoms of vitamin D3 poisoning will be taught to them and they will be asked to discontinue the supplements and inform the researcher if the signs of intoxication are detected. Any side-effects will be reported at the end of study.

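### Because each suppository arm shares one letter, telling the researchers what one woman received would unblind them to every suppository user

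*Protocol article*

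**What the plan says.** The Blinding section of the protocol article describes the coding. The two products look alike and "will coded as A and B by a pharmacologist not involved in the research team". It continues: "The researchers will receive the suppositories with codes and will not know what A and B stands for with respect to the suppositories". The key is opened at the end: "Finally, after collecting questionnaires and analyzing data using SPSS version 25 software, the codes that belong to the groups will be determined".

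Three other sections bear on this.

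- **Safety issues.** Women are taught the signs of vitamin D3 poisoning, and "they will be asked to discontinue the supplements and inform the researcher if the signs of intoxication are detected".
- **Intervention program and patient education.** The researcher teaches each woman how to use the product, gives her a telephone number for questions and local symptoms, and monitors use by telephone or text message for 8 weeks. The suppositories are handed over "without identifying the type of suppository, only having an identifier code inside the appropriate envelopes". The section does not say whether this identifier is the arm letter or a code belonging to one woman.
- **Randomization.** The allocation sequence uses letters whose meaning is printed: "A (suppository of vitamin D3 group), B (placebo suppository group), and C (control group without intervention".

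On size, the abstract states that "105 postmenopausal women will be randomly assigned to three groups", and the sample size section that "the sample size for each group was calculated to be 35 people".

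**The concern.** Under an arm-wide letter code, everyone in an arm shares the same secret. The people who hold the lettered supplies are on the same team as the person who takes reports of suspected intoxication. If such a report led the pharmacologist to tell that team what one woman was using, the team would know what her letter means and, by elimination, the other letter too.

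Vitamin D versus placebo is the only comparison that the article tries to blind, since the no-intervention group cannot be blinded. The outcome is the FSFI, a questionnaire of women's own answers, taken immediately after treatment and 1 and 2 months later. A researcher who knew the arms would still be phoning or texting women during treatment and would be on the team running the follow-up. The team would also analyse the data. The data analysis section leaves it to the data whether to transform and whether to move to a mixed model or non-parametric tests. Those choices are better made without knowing which arm is which.

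**Working it through.** No formula in the plan is at issue. The check is to read the sections together and count the women affected.

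**Step 1. What the researchers hold.** Blinding: supplies lettered A or B, without the meaning. They can therefore tell which women share a letter, but not which product the letter denotes.

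**Step 2. What one disclosure adds.** There are two products and two letters. If the researchers learn that one woman, holding letter X, received a given product, then X denotes that product and the other letter denotes the other product. One answer settles both arms.

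**Step 3. How many women that covers.**

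- Planned size per arm: 35 (Sample size estimation).
- Arms: 3. Check: 3 × 35 = 105, which agrees with the abstract.
- Suppository arms: 2. Women exposed: 2 × 35 = 70, or 70/105 = 67% of the trial and 100% of the blinded comparison.
- Allocation is by simple randomization, so the realised number will vary. Assuming equal allocation probabilities, the standard deviation of the number of suppository users is √(105 × 2/3 × 1/3) = 4.8. Hence about 70.

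**Step 4. Who would have to be told.** The count in step 3 applies only if the answer reaches people who know the other women's letters.

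| Who learns one woman's product | Two arm-wide letters | Unique pack numbers |
|---|---|---|
| Research team | Arm of about 70 women | Arm of 1 woman |
| Clinician outside the team, who does not know other women's letters | Arm of 1 woman | Arm of 1 woman |

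The coding method matters in the first row. The reporting route in Safety issues leads to the researcher, so that row is a realistic one.

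**Step 5. Does it depend on the letters printed under Randomization?** No. Steps 1 to 3 assume that the researchers do not know the meaning of A and B at the outset. Choosing different letters for the products would leave the result unchanged, because there would still be two of them.

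**The case against.** Much of the case on the other side stands.

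- **Omission from an article.** An emergency code-break procedure is commonly left to the full protocol, which is not shown. Its absence here is no finding. The arm-wide lettering, however, is stated, and any such procedure would have to work with it.
- **No contradiction between blinding and safety.** A reader might infer that the late opening of the key and the stop-and-report rule cannot both be kept, or that a woman cannot be unblinded without unblinding everyone. The text does not support either. Stopping and reporting do not require the allocation to be known. The Blinding section describes the routine end of the blind and does not forbid an individual disclosure. The pharmacologist is outside the team and could inform the woman or a treating clinician alone.
- **Individual codes may exist.** The identifier in the envelope could be individual, and the questionnaires are numbered in sequence. But the Blinding section names only A and B for the products, so the two sections need to agree.
- **No rate.** A reader might want the chance of at least one code break, 1 − (1 − q)^70 for a fraction q of suppository users. This gives about 7% at q = 0.1%, 51% at 1% and 76% at 2%. The answer is set entirely by an assumed q. It also supposes that every report leads to a disclosure to the researchers. The article gives no rate and considers poisoning unlikely, so none of these figures is evidence.
- **Limited harm.** The women themselves would stay blind if only the researchers learned a letter. The loss is of researcher blinding, which is less than loss of the whole blind.
- **A firmer problem nearby.** The Randomization section prints the meaning of A and B, while the Blinding section says the researchers do not know it. A reader might infer that the blind is open from the start. That would follow only if the letters are the same and the researchers know the sequence key, and the article settles neither. The two sections must be reconciled in any case.

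**Conclusion.** The concern holds in a limited form. With two arm-wide letters, any disclosure to the researchers of what one woman received reveals the arm of about 70 of the 105 women and ends researcher blinding for vitamin D versus placebo. Disclosure by the pharmacologist to a clinician outside the team would not.

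This rests on the Blinding section as written: one letter per product, with the researchers holding the lettered supplies. If the identifier in the envelope is in fact unique to each woman, and the researchers never see the letters, the point falls away and only the wording needs correcting.

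The consequence of one disclosure is fixed by the coding method. How likely it is cannot be estimated from the article. It is a cheap improvement to a stated method, not an error that invalidates the design.

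**What to change.** In the Blinding section, replace the A/B product letters with a unique pack number for each woman, unrelated to arm and different from the A/B/C key printed under Randomization. The outside pharmacologist keeps the list linking numbers to products, and one sealed code per woman. Any single code break, under whatever procedure the full protocol sets, then exposes only that woman. The group key stays closed until the analysis is done.

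Three details make this work:

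- The allocation envelopes should give the researchers a pack number or the no-intervention assignment, not an arm letter.
- The section on the intervention program and patient education should state that its identifier is this pack number.
- The blinded analysis needs neutral group labels. These should be released only after data collection, and whoever analyses the data should not be told the result of any individual code break, because one known woman would give the label away.

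Cost: labels and sealed slips for about 70 packs, prepared by the pharmacologist already involved, and a few changed sentences. The downside is that a few women may be individually unblinded.

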### Intervention

After selecting the participants and random allocation to the groups, the participants’ sexual function will be assessed before the intervention. The participants in the treatment group will receive the vitamin D3 suppository and the placebo group will receive placebo suppositories identical the vitamin D3 suppositories in appearance. No intervention will be performed in the control group.

The use of vitamin D3 and placebo vaginal suppositories are consistent with the protocol used in the study by Rad et al. [24]. For 8 weeks, a single dose of 1000 unit vitamin D3 will be taken every night for the first 2 weeks, and every other night for the following 6 weeks. The reason for the choice of dosage and similar therapeutic protocol is because of the significant results reported in the improvement of para-clinical symptoms of vaginal atrophy based on the Pap smear. Since the results of this treatment have not been evaluated clinically, a similar dose is chosen for this study to examine the effect of vaginal vitamin D on sexual function.

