### Recruitment

To recruit the participants, eligible individuals will be selected on the basis of information in the health records of the comprehensive health centers in the city of Buin Zahra. A total of 105 eligible individuals will be invited to participate in the study. After screening the eligible individuals based on their health records, they will be called and invited for a visit in their comprehensive health care center. When they come for the screening visit, they will interviewed to assess eligibility criteria, introducing the project, its’ aim, their autonomy to participate in the study, confidentiality and anonymity of collected data. After signing the written consent, they will be randomized to study groups.

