### Primary outcome measurements

Sexual function will be the primary outcome measure,. This will be assessed using the Female Sexual Function Index (FSFI). The FSFI comprises 19 questions of sexual function in six independent areas consisting of desire (two questions), arousal (four questions), lubrication (four questions), orgasm (three questions), sexual satisfaction (three questions) and pain from sex (three questions). Responses to the desire items are made on a six-point Likert scale from 0 (*never*) to 5 (*completely*) with a minimum score of 1 and a maximum score of 6. For other areas, responses are also made on a six-point Likert scale from 0 (*none*) to 5 (*completely*) with a minimum score of 0 and a maximum score of 6 [33]. The validity of the Persian version of this scale was evaluated and validated by Mohammadi et al. [34].

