### Baseline assessments

Evaluation of sexual function in postmenopausal women will be performed among all three groups at the beginning of the study and before the intervention.

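### The baseline FSFI is scheduled after random allocation, with nothing stated to keep the allocation hidden until it is complete, so women in the unblinded control arm may know their assignment when they report it

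*Protocol article*

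**What the plan says.** Three sections of the protocol article fix when the baseline is taken.

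- **Recruitment**, at the end of the screening visit: "After signing the written consent, they will be randomized to study groups". No FSFI is placed between consent and randomisation.
- **Intervention**: "After selecting the participants and random allocation to the groups, the participants’ sexual function will be assessed before the intervention".
- **Baseline assessments**: the evaluation "will be performed among all three groups at the beginning of the study and before the intervention".

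Two sections bear on who may know the assignment at that time.

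- **Blinding**: "Due to having a control group which receives no intervention, blinding cannot be performed for all groups". Only vitamin D and placebo are masked, by suppositories alike in colour and shape and coded by someone outside the team. The Intervention section adds: "No intervention will be performed in the control group".
- **Randomization**: "The type of intervention will be written in accordance with the assignment sequence and will be enclosed within the opaque envelopes". Questionnaires are numbered in the same sequence, so that "the questionnaire with the same code will be completed for the person receiving the code 1 intervention". When an envelope is opened relative to the questionnaire is not said.

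The baseline score is used. The first objective under Goals and hypotheses compares scores within each arm starting from the pre-intervention value. Data management and analysis plans a repeated-measures ANOVA of the sexual function scores.

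**The concern.** A baseline can serve as a neutral reference only if the assignment cannot influence it. Randomisation guarantees this when the measurement comes before allocation, and masking largely guarantees it when the measurement comes after. Here the measurement comes after allocation, and for one of the three arms there is no masking. The outcome is a self-completed scale on an intimate subject, where expectation or disappointment could plausibly move the answers.

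If knowing the assignment moved the control arm's baseline, the error would enter that arm's change over time and any group-by-time comparison with it. It could hide an effect or create one. The data would not show it clearly, because at baseline a shift due to knowledge cannot be told apart from chance imbalance. It could not be repaired after enrolment.

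**Working it through.** **Sequence.** The article gives no figure on this point to reproduce, so the first check is of the text. Recruitment puts randomisation directly after consent. Intervention puts the FSFI after allocation. Baseline assessments puts it before treatment, which fits the same order: a measurement can be before treatment and still after allocation. No section places the FSFI before allocation, and none says the envelope stays sealed until the questionnaire is done. The order is therefore stated; the moment of disclosure is not.

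**Which comparisons are exposed.**

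- Vitamin D versus placebo: both arms receive matched, coded suppositories, so knowledge of assignment should not move their baselines apart. Largely protected.
- Change within the control arm: exposed.
- Group-by-time contrasts of either suppository arm with control: exposed.
- Comparison of post-treatment scores only, as the second objective is worded: baseline does not enter, so this bias does not arise.

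**Size, as an illustration.** The documents give no figure for a shift. Assume that knowing the assignment moves the control arm's reported baseline by b = 0.1 to 0.3 SD, and that a fraction k of this persists at follow-up.

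- Under the stated order, bias in the control arm's change = k·b − b = −(1 − k)·b.
- With k = 0 (baseline only), its absolute size is b, so the contrast with control is biased by 0.1 to 0.3 SD.
- With k = 1 (full persistence), it is zero.

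For scale, 0.1/0.6 = 17% and 0.3/0.6 = 50% of the effect size of 0.6 in Sample size estimation, although that section does not say which contrast 0.6 describes.

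For k = 0, no true effect and n = 35 per arm, take the baseline to follow-up correlation r as 0.5 or 0.7 (also an assumption). The standard error of the difference in change, in SD units, is √[(2/n)·2(1 − r)]:

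- r = 0.5: √[(2/35)·1.0] = 0.239
- r = 0.7: √[(2/35)·0.6] = 0.185

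Two-sided error at nominal 5% = Φ(−1.96 + b/SE) + Φ(−1.96 − b/SE):

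| Shift b (SD) | r = 0.5 | r = 0.7 |
|---|---|---|
| 0.1 | 7% | 8% |
| 0.2 | 13% | 19% |
| 0.3 | 24% | 37% |

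These are values for one scenario (k = 0), not predictions. A test of the group main effect averaged over all four occasions would carry only b/4, that is 0.1/4 = 0.025 to 0.3/4 = 0.075 SD.

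**The case against.** **Disclosure may come after the FSFI.** A reader might infer that control women already know they will receive nothing when they fill in the baseline. The article does not say so. Assignments sit in opaque envelopes, and suppositories are handed over at the first visit in coded envelopes. Revealing the arm at that moment, after the questionnaire, is compatible with the text. This stands: the defensible wording is that they may know. The concern survives, because the article states an order that puts allocation first and gives no safeguard.

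**Not every comparison is affected.** A reader might extend the problem to all comparisons from baseline. The masking of the two suppository arms does not support that, and the between-group objective lists only post-treatment times. The article specifies neither change scores nor baseline adjustment, so a claim about a contaminated covariate would concern an analysis that is not planned. Baseline still enters the within-group objective and can enter the repeated-measures model.

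**The shift is unsourced and may persist.** Control women stay unblinded throughout. If disappointment lowered their reports equally at every visit, it would cancel from the change under the present order, whereas a clean baseline would leave the follow-up part in. This is correct, and it is why the figures hold only for a shift confined to baseline. It also means the fix does not cure unblinded reporting at follow-up. It is no reason to keep the order, since relying on two unknown biases to cancel is not a design.

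**Loss of baselines.** One might add that women who leave on learning their arm would have no baseline. That again presumes disclosure before the FSFI, so it is a possibility rather than a finding.

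**Conclusion.** The point holds in a limited form. The stated order is consent, allocation, baseline FSFI, and nothing in the article keeps the allocation concealed until the FSFI is complete. With an arm that cannot be blinded and a self-reported outcome, this leaves the control arm's baseline open to knowledge of assignment. At risk are the within-group change in that arm and the group-by-time contrasts with it.

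The article does not show that the baseline is in fact unblinded, and the size and direction of any shift are unknown. The range of 0.1 to 0.3 SD in the change contrast with control rests on two assumptions: a shift of that size, and its absence at follow-up. The case for acting rests on the order of steps and on how little it costs to change, not on that range.

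**What to change.** In Recruitment, Intervention and Baseline assessments, state one sequence: eligibility confirmed, consent signed, coded baseline FSFI completed, then the next envelope opened and the allocation revealed, all at the same visit. If the envelopes are already meant to stay sealed until the questionnaire is done, saying so in these sections is enough.

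The cost is wording and the order of steps within one visit. Questionnaire, staff and sample size are unchanged. With the FSFI completed before disclosure, the expected baseline shift due to assignment is zero. The change has to be in place before the first woman is randomised, because a baseline taken in the wrong order cannot be corrected afterwards.
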